### Predictors and moderators of response to internet-based psychotherapy

CBT and IPT are reported to have similar effectiveness in reducing depressive symptoms [44–47]. Donker et al. concluded that, even when treatments are determined equally effective, there are individual characteristics (gender, age, education level, marital status, baseline depression level, coping skills, and previous depression) that influence treatment outcomes [28]. Individual characteristics that influence treatment effectiveness can be broken down into predictors and moderators [28]. Both predictors and moderators are considered pretreatment variables; however, the predictors forecast mental health outcomes in the intervention groups, while moderators identify persons more likely to benefit from particular treatments [28]. Examples of predictors of the efficacy of internet-based interventions include whether the internet-based therapies (CBT, IPT) are guided [28, 48], being female, obtaining low mastery scores on self-mastery measures and low dysfunctional attitudes on coping questionnaires [28]. A moderator of internet-based therapy is age, with evidence indicating that older adults benefit from CBT and younger adults demonstrate larger improvements with IPT [28]. A moderator of IPT is also a role transition, with role transitions occurring in younger adults of childbearing years [28]. Individuals undergoing role transitions are thought to benefit more from internet-based IPT because of the foci of IPT; specifically, interpersonal conflicts and role transitions are particularly relevant in their stage of life [28, 49]. As a result, it is expected that younger adults navigating a significant role transition (e.g., being pregnant and becoming a mother) would benefit from guided, internet-based IPT to improve symptoms of depression, anxiety, stress and interpersonal functioning [50].

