1	To evaluate the clinical effectiveness of online interpersonal psychotherapy versus routine care on reducing stress, anxiety, and depression in prenatal women	What is the effect of an online interpersonal psychotherapy intervention compared to routine care on the percentage of prenatal women with symptoms of stress, anxiety, and depression?	The percentage of prenatal women with stress, anxiety and depression about the clinical cut-offs of validated tools will be significantly lower in the intervention group versus routine care
2	To evaluate the effectiveness of the online interpersonal psychotherapy intervention compared to routine prenatal care on relationship distress	Is relationship distress reduced in the online interpersonal psychotherapy intervention group compared to the routine prenatal care control group?	Relationship distress will be significantly reduced in the online interpersonal psychotherapy group
3	To identify factors, mediators and moderators that are associated with effectiveness of the intervention among participants within the intervention group	What factors, mediators, and moderators are associated with the intervention effect?	Among participants in the intervention group, no factors will be significantly associated with the intervention effect, indicating that online interpersonal psychotherapy is appropriate for prenatal women

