##### Variables

Variables that are associated with (and may mediate) the effectiveness of the e-IPT will be explored through an examination of variables that may be influential in the perinatal mental health theories and literature. The factors to be included were selected based on their association with perinatal depression, anxiety and stress. As a result, the influence of self-efficacy, social support, sense of mastery, self-esteem, sleep, coping, and resilience will be explored. Additionally, the association of preconception of mental health problems such as borderline personality disorder, perfectionism, and attention deficit/hyperactivity disorder will be investigated. These variables will be included as covariates in the data analysis models.

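### Secondary objective 3 looks for mediators and moderators of the e-IPT effect inside the e-IPT arm only, and treats non-significance as indicating that e-IPT is appropriate

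*Protocol article*

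**What the plan says.** Table 2 of the protocol article (under Research objectives, questions, and hypotheses) states secondary objective 3 as: "To identify factors, mediators and moderators that are associated with effectiveness of the intervention among participants within the intervention group". The matching hypothesis repeats the restriction to the e-IPT arm and expects that "no factors will be significantly associated with the intervention effect, indicating that online interpersonal psychotherapy is appropriate for prenatal women".

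The background section on predictors and moderators separates two ideas: "the predictors forecast mental health outcomes in the intervention groups, while moderators identify persons more likely to benefit from particular treatments". It gives an example of the second kind: "A moderator of internet-based therapy is age".

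The Variables section lists the candidates. It says that "the influence of self-efficacy, social support, sense of mastery, self-esteem, sleep, coping, and resilience will be explored", which is seven factors, and that the association of earlier problems such as "borderline personality disorder, perfectionism, and attention deficit/hyperactivity disorder will be investigated", which adds three. These enter the models as covariates. The Quantitative analysis section screens them by bivariate significance and plans intention-to-treat analysis with multiple imputation.

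The section on the control condition has the control women complete the same questionnaires at the same times as the e-IPT women.

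**The concern.** An intervention effect is a difference between arms. Where everyone receives e-IPT, a woman's outcome reflects both how she would have fared anyway and what the programme added, and nothing in that arm separates the two. A factor that only marks prognosis can then be taken for a modifier of benefit, and a real modifier can go unseen.

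The hypothesis adds a second problem. It makes a null result favourable to the therapy, so the less power the analysis has, the more likely the favourable reading becomes. Even a true absence of associated factors would say nothing about appropriateness: a programme that helps nobody shows no moderators, and a programme that helps some women more than others may still be appropriate.

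The pilot is meant to inform a full trial. Statements about who benefits, or that e-IPT suits prenatal women in general, could be carried forward without support.

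**Working it through.** The protocol gives no power or sample size for objective 3, so there is no stated figure to reproduce. Correlations, interaction sizes, the 50/50 factor and independence of tests are assumptions.

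**Inputs from the protocol**
- 80 women per arm, 160 in total; 25% attrition and 5% loss to follow-up (Sample size estimation). The two rates are stated for the full trial. Applied here: 80 × 0.75 × 0.95 = 57.
- All 80 would nominally be analysed under intention-to-treat with multiple imputation (Quantitative analysis). Hence the range 57 to 80.
- 7 + 3 = 10 candidate factors (Variables).
- Two-sided 5% level and 80% power, the conventions of the main calculation.

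**1. What one arm can identify.** Write outcome = b0 + b1·X + b2·A + b3·A·X + error, with A = 1 for e-IPT and 0 for routine care.
- Slope of X in the control arm: b1 (prognosis).
- Slope of X in the e-IPT arm: b1 + b3.
- Moderation: b3, the difference between the slopes.

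The e-IPT arm alone gives only the sum b1 + b3. For mediation, the effect of allocation on the mediator is itself a difference between arms and cannot be estimated from one.

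**2. Size of the error.** Simulation with 20,000 runs per scenario, normal factor and outcome, two-sided 5% tests:

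| Scenario | Women per arm | Within-arm test significant | Arm-by-factor test significant |
|---|---|---|---|
| Prognostic only, r = 0.2, no treatment effect | 80 | 43% | 5% |
| Prognostic only, r = 0.3, no treatment effect | 80 | 78% | 5% |
| Prognostic only, r = 0.4, no treatment effect | 80 | 96% | 5% |
| Prognostic only, r = 0.3, no treatment effect | 60 | 66% | 5% |
| Slope 0.3 cancelled in the e-IPT arm by true moderation | 80 | 5% | 50% |
| Slope 0.4 cancelled in the e-IPT arm by true moderation | 80 | 5% | 77% |

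The within-arm test flags prognosis when there is no moderation, and misses moderation that offsets prognosis.

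**3. What a within-arm null is worth.** Fisher z: power ≈ Φ(atanh(r)·√(n − 3) − 1.96). Smallest r with 80% power: tanh((1.96 + 0.84)/√(n − 3)).

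| | n = 57 | n = 80 |
|---|---|---|
| Smallest r with 80% power | tanh(2.80/√54) = 0.36 | tanh(2.80/√77) = 0.31 |
| True r = 0.20 missed | 68% | 57% |
| True r = 0.30 missed | 38% | 22% |

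**4. Chance findings.** If the ten factors were independent and none mattered, the chance of at least one p < 0.05 on one outcome is 1 − 0.95^10 = 0.40. The hypothesis could therefore fail by chance as well as succeed through low power.

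**5. What both arms would give.** For a 50/50 binary factor the interaction has standard error √(16/N) SD. The size detectable with 80% power is 2.80 × √(16/160) = 0.89 SD with all 160 women, and 2.80 × √(16/114) = 1.05 SD with 114 (2 × 57). Power for an interaction of 0.5 SD is 35% and 27% respectively.

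**The case against.** Several points on the other side stand.

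- **Part of the objective is sound.** Factors that forecast outcome can properly be studied within one arm, and the background defines predictors that way. Number of modules completed exists only in the e-IPT arm. A reader might infer that all of objective 3 is invalid; only the mediator and moderator parts are.
- **The wording is soft.** A reader might infer that the plan treats a null result as proof. It says that the result would indicate appropriateness, and the Variables section speaks of exploring. The inference is still wrong in the softer form.
- **The background does not state the two-arm requirement.** It separates predictors from moderators but does not say that a moderator needs a control arm, and it does not define mediators. That requirement is general methodology. Its age example does compare two therapies, so it does not directly contradict a hypothesis about e-IPT against routine care.
- **The figures depend on assumptions.** Using 57 women alone would show only the unfavourable end. The 40% is an illustration: self-efficacy, mastery, self-esteem, coping and resilience are related, which lowers it for a single outcome, while several outcomes would raise it.
- **Models may be specified elsewhere.** An analysis plan may describe interaction or mediation models, so their absence from the article carries no weight. The point rests on what Table 2 states, and such models would have to depart from its restriction to one arm.

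**Conclusion.** The concern holds for the mediator and moderator parts of secondary objective 3 and for the inference attached to its hypothesis. As written, a factor that is only prognostic, with r between 0.2 and 0.4, would be significant in 43% to 96% of trials with 80 e-IPT women and no moderation. A null result would be weak evidence of no association and no evidence of appropriateness. Covariate adjustment after a bivariate screen does not repair this, because it does not estimate how the effect differs between women.

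The weight is moderate. A reader might infer that the pilot's main conclusion is compromised; the documents do not support that. The primary outcome is feasibility and acceptability, and neither that nor randomisation nor data collection depends on objective 3. The wording can be corrected at any time before analysis. The structural argument needs no numerical assumption; the percentages rest on those stated in the working.

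**What to change.** Reword objective 3 in Table 2 and align the Variables and Quantitative analysis sections:

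1. Keep within-arm associations, but call them predictors of outcome among women offered e-IPT.
2. Assess moderators by arm-by-factor interaction, and mediators with allocation as the exposure, using both arms.
3. Use DASS21 and EPDS scores as pre-randomisation moderators. The Both groups section that follows the control condition places only these two before randomisation. The T1 battery comes afterwards, and the randomisation section has women told their allocation at once. Flag T1 variables accordingly, unless they are stable characteristics such as age. The Data collection section labels T1 as recruitment, so the timing should be stated consistently.
4. Report estimates with 95% confidence intervals, labelled exploratory.
5. Delete the clause that non-significance indicates that e-IPT is appropriate.

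The cost is rewording and some added analysis. No new data are needed, because the control women already complete the same questionnaires. The drawback is imprecision: the two-arm analysis cures validity, not power, so a null interaction in the pilot remains uninformative and the conclusions must be more modest.

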## Methods/design

This protocol is reported according to the Standard Protocol Items: Recommendations for Interventional Trials guidelines (Fig. 1).

**Fig. 1. Fig1:**
[figure not shown]
SPIRIT schedule of enrollment, interventions, and assessments

### Study design

This pilot study is a randomized controlled trial of two parallel groups. The intention of this study is to evaluate the feasibility and acceptability of IPT in a online format for a sample of prenatal women. Additionally, this study is a parallel group, Consolidated Standards of Reporting Trials revised 2010 compliant, pilot randomized controlled trial of e-IPT versus routine prenatal care (Fig. 2). Data collection points are at baseline, 3 months postrandomization, and at 3 and 6 months postpartum. The current trial protocol has been approved by the Conjoint Health Research Ethics Board at the University of Calgary (REB16–0061). This study is registered with ClinicalTrials.gov (identifier NCT1901796).

**Fig. 2. Fig2:**
[figure not shown]
Consolidated Standards of Reporting Trials 2010 flow diagram. DASS21 Depression, Anxiety, and Stress Scale-21, EPDS Edinburgh Postnatal Depression Scale

### Participants

Pregnant women will be recruited through established recruitment sources including maternity clinics, posted announcements and pamphlets available in the main areas of family medical clinics and other areas that pregnant women frequent (e.g., health centers, antenatal clinics, prenatal classes, hospitals). Participants will also be recruited through online advertising and media outreach.

Health-care providers will ask eligible pregnant women if they would like to participate in this study and will provide these women with a study postcard containing the link to the online study web application. The study postcard will also contain contact information for the research coordinator who is available to answer any outstanding questions for participants.

### Inclusion and exclusion criteria

Eligible participants are women who reside in Alberta, Canada, are over the age of 18 years and are pregnant, from conception to 30 weeks gestation. Participants must be able to read and write in English. Participants must be capable of providing informed consent and of learning and understanding new information such as contained in the e-IPT modules. Additionally, participants must have access to online hardware including a digital device (either a computer, smart phone, or tablet).

### Screening, consent, and enrollment

Study postcards containing the link to the online study web application will be provided to potential participants. The link to the online study web application will describe the nature of the study, the study protocol, and randomization procedures. If participants are interested, they will electronically consent to participate by responding affirmatively to a single-step consent process on the online consent form. Participants will also be contacted by email and asked if they would consent to a telephone interview about the acceptability of the intervention after they have completed the 3-month postpartum questionnaire.

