**Methods:**

A pilot randomized controlled trial design with repeated measures will evaluate the feasibility and acceptability of e-IPT for pregnant women compared to routine prenatal care. Qualitative interviews with 15–30 individuals in the intervention group will provide further data on the feasibility and acceptability of the intervention. Assessment of feasibility will include the ease of accessing and completing the intervention. Women will also be asked about what barriers there were to starting and completing the e-IPT. Assessment of acceptability will inquire about the perception of women regarding the intervention and its various features. A sample size of 160 consenting pregnant women aged 18 years and older will be enrolled and randomized into the experimental (e-IPT) or control (routine care) condition. The secondary outcome measures include: depression, anxiety and stress symptoms; self-efficacy; self-mastery; self-esteem; relationship quality (spouse, immediate family members); coping; and resilience. All participants will complete the aforementioned measures at baseline during pregnancy (T_1_), 3 months postrandomization (T_2_), at 8 months of pregnancy (T_3_), and 3 months postpartum (T_4_).

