### Both groups

All applicants will complete the Depression, Anxiety, and Stress Scale-21 (DASS21) and the Edinburgh Postnatal Depression Scale (EPDS) on recruitment (prerandomization) to provide baseline data on their mental health status. All participants (control and intervention groups) assessed as having thoughts of self-harm will receive a computerized message offering then crisis line/emergency room contact information and informing them that they will be contacted by the study nurse. Following randomization, participants will complete the baseline series of questionnaires which comprehensively assess a variety of demographics and psychosocial constructs (T_1_) (Fig. 1). These questionnaires will be completed again at 3 months postrandomization (T_2_), after 8 months of pregnancy (T_3_), and 3 months postpartum (T_4_).

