### Data analyses

#### Feasibility and acceptability of the intervention

Feasibility and acceptability, in addition to the qualitative data obtained from the interviews, will be characterized using descriptive statistics (frequencies, proportions, means, standard deviations). Feasibility will be assessed as the rate of retention in the study and percentage of modules completed. The acceptability of this intervention will consist of an analysis of the perceptions of the prenatal women regarding the intervention and its various features. Acceptability will be assessed by open-ended questions exploring the reported ease for women in navigating the online intervention. Participants will also be asked about what was useful and that was difficult in navigating this online intervention. The qualitative data will be analyzed using inductive thematic analysis. This method was chosen because it allows patterns and key themes within the data to be identified [76]. The three-stage process of thematic analysis will involve: 1) generating code; 2) merging and renaming similar codes; and 3) grouping codes into overarching themes that best describe the data [77].

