### Trial status

This study, protocol version V.1, dated 24 May 2019, commenced recruitment in March 2019. This pilot study will be performed over a 6-month period. We will disseminate trial results through research articles.

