## Data Availability

Participants will complete questionnaires online and these data will be sent to a secure Canadian Amazon server. There the data will be anonymized and then downloaded to a secure server at the Health Research Data Repository (HRDR), housed in the Faculty of Nursing, University of Alberta. Additionally, the data will be stored and analyzed within the HRDR. HRDR access is restricted to the research team conducting data analyses. Qualitative interviews will be digitally recorded and transcribed verbatim. These transcribed interviews and digital files will be password protected and stored on a password-protected computer in a locked, secure office at the University of Calgary. We expect to complete feasibility and acceptability interviews by October 2019.

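### The feasibility and acceptability interviews are open only to women who complete the 3-month postpartum questionnaire, so women who leave cannot report barriers, and few can reach that point by October 2019

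*Protocol article*

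**What the plan says.** Interview timing is given in one place only. Under Screening, consent, and enrollment, women are to be "asked if they would consent to a telephone interview about the acceptability of the intervention after they have completed the 3-month postpartum questionnaire". The Abstract, Both groups and Data collection sections make 3 months postpartum the final questionnaire, T4. Data collection sets 30 interviews; the Abstract says 15–30.

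The interviews are meant to reveal difficulties. The Abstract states: "Women will also be asked about what barriers there were to starting and completing the e-IPT". Primary outcomes uses them for ease of access and completion and for suggested improvements, and the analysis section adds what was difficult.

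On dates, Trial status says the study "commenced recruitment in March 2019" and "This pilot study will be performed over a 6-month period". Data Availability says: "We expect to complete feasibility and acceptability interviews by October 2019". Eligible women are "pregnant, from conception to 30 weeks gestation".

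**The concern.** Whether the phrase about the 3-month postpartum questionnaire governs the invitation or the interview itself, T4 must be completed first. Women who leave the study before then are well placed to say what made e-IPT hard to continue, yet they have no described way into the interviews. The only primary hypothesis in Table 1 is that women will define how to improve e-IPT before a full trial, so the gap touches the main product of the pilot.

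The dates add a second selection. T4 lies months after entry for every woman and nearly a year after entry for those who join early in pregnancy. If interviews end in October 2019, the pool consists mostly of women who enrolled soon after opening and were already well advanced in pregnancy.

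**Working it through.** **Inputs from the protocol.** e-IPT arm 80; attrition 25% and loss to follow-up 5% (Sample size estimation); entry up to 30 weeks; recruitment from March 2019; interviews complete by October 2019; T4 at 3 months postpartum; target 30, or 15–30.

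**Assumptions.** Birth at 40 weeks (39 as a variant); 3 months = 13 weeks; 1 March and 31 October as the most favorable dates; even accrual; gestation at entry spread evenly over the stated range. The 25% and 5% are full-trial planning figures, applied here to the pilot arm.

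**1. Women who reach T4 at all.** 80 × 0.75 × 0.95 = 57, so 80 − 57 = 23 do not. Adding the two losses instead gives 80 × 0.70 = 56, so 24 do not.

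**2. Time from entry to T4.** Weeks = (40 − gestation at entry) + 13 = 53 − gestation at entry. At the 30-week limit this is 23 weeks; at 12 weeks it is 41.

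**3. Who can reach T4 in time.**
- 1 March to 31 October is 34.9 weeks. A woman enrolled on 1 March needs 53 − 34.9 = 18.1 weeks of gestation or more. For 1 October (30.6 weeks) she needs 22.4.
- A woman at 30 weeks must enroll by 23 May for 31 October, or by 23 April for 1 October.
- A woman enrolled on 1 March at 12 weeks reaches T4 on 13 December 2019.
- If the six months cover the whole study (26.1 weeks), even a woman enrolled on the first day needs 53 − 26.1 = 26.9 weeks.

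**4. Expected number available by 31 October.** A woman enrolled t weeks after 1 March needs gestation of at least 18.1 + t. Nobody qualifies beyond t = 30 − 18.1 = 11.9. When the lowest entry gestation is below 18.1, the qualifying share is (11.9²/2) ÷ (gestation range × accrual weeks). For entry at 12–30 weeks over 26 weeks this is 70.3 ÷ (18 × 26) = 0.15, or 12 of 80; multiplied by 0.75 × 0.95 it leaves 9. For entry at 20–30 weeks everyone qualifies for the first 1.9 weeks, so the area is 1.9 × 10 + 10²/2 = 69, and 69 ÷ (10 × 26) = 0.26, or 21 of 80, leaving 15.

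| Accrual | Entry gestation | Reach T4 in time, of 80 (birth at 40 / 39 wk) | After 25% and 5% losses |
|---|---|---|---|
| 6 months | 4–30 wk | 8 / 10 | 6 / 7 |
| 6 months | 12–30 wk | 12 / 14 | 9 / 10 |
| 6 months | 20–30 wk | 21 / 24 | 15 / 17 |
| 3 months | 4–30 wk | 17 / 20 | 12 / 14 |
| 3 months | 12–30 wk | 24 / 28 | 17 / 20 |
| 3 months | 20–30 wk | 42 / 48 | 30 / 34 |

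These counts come before any refusal of interview. With six-month accrual and a later start or earlier end within the stated months, about 1 to 11 of 80 reach T4 before losses.

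**The case against.** The strongest reply is that the interviews are one strand among several. The primary outcome also covers enrollment, retention, adherence to data collection and delivery, and modules completed, which the application records automatically. Those measures include women who leave. Intervention women also answer rating questions whose timing is not stated. This stands: a reader might infer that the whole primary outcome hears only from retained women, and the protocol does not support that.

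Three further inferences also fail.
- That women who never started e-IPT are shut out. The gate is a questionnaire, not a module; a woman with no modules who completes T4 can be interviewed.
- That acceptability yields no percentage because "Acceptability will be assessed by open-ended questions exploring the reported ease for women in navigating the online intervention". The same section plans frequencies and proportions, and Primary outcomes defines acceptability as percentages of the intervention group.
- That women enrolling early in pregnancy are the likeliest to drop out. Nothing in the protocol says so.

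On the calendar, October 2019 is worded as an expectation, and the protocol does not say whether six months means recruitment or the whole study. If interviews simply run later, the calendar selection disappears. That is fair, but the stated date and period would then need changing, and the T4 gate would remain.

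**Conclusion.** The point holds for the interview strand. About 23 of 80 e-IPT women would be unable to contribute under the protocol's own loss figures. The stated dates, entry window and interview target do not realistically fit together. On the most favorable dates with six-month accrual, 6 to 17 women would be available. Thirty is reached only if everyone enrolls within three months from 1 March, all at 20–30 weeks, with hardly any refusals. The lower target of 15 is reached in some of the favorable scenarios. The counts rest on the assumed birth week, even accrual and spread of entry gestation; the 23-week minimum rests only on a 40-week birth and 13 weeks to T4.

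A reader might go on to put a figure on bias in the acceptability percentage. The documents do not allow it: they give no acceptability rate and do not tie the rating questions to T4. An optimistic tilt in the interviews is plausible but not shown.

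**What to change.** - **Invitation.** Draw interviewees from all randomized e-IPT women whether or not they complete questionnaires: for example once T2 is due, or at the T4 due date or on stopping. Sample across modules completed (0, 1–5, 6). The number of interviews need not change.
- **Percentages.** Report those defined under Primary outcomes with all 80 randomized e-IPT women as denominator, and show non-response.
- **Dates.** Reconcile Screening, consent, and enrollment, Data collection, Trial status and Data Availability. If recruitment runs to 31 August 2019, a woman entering that day reaches T4 on 8 February 2020 if at 30 weeks, and on 8 August 2020 if at 4 weeks. With a T2 trigger, everyone enrolled by 1 August is due by 31 October: under even accrual over 26 weeks that is 21.9/26 = 84%, about 67 of 80.

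Costs: recruitment has already begun, so this changes procedure as well as text. Women who have left are harder to reach. Interviews before T4 could slightly influence later answers. For a woman entering at 30 weeks, T2 falls at 30 + 13 = 43 weeks, about three weeks after a 40-week birth, which is a burden and a reason to allow the later trigger.
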